# **Outcome measures:**

# The main outcome will be the effectiveness of neural mobilization technique on pain intensity measured on VAS, endurance measured by cranio cervical flexion test and range of motion measured on inclinometer. Secondary outcomes will be to see the effectiveness of conservative treatment and measuring the effects of treatment on quality of life [^24^](#_ENREF_24).

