## Neck disability index (NDI):

Neck disability will be assessed by using neck disability index [^24^](#_ENREF_24).

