**Heart Disease:** Yes/No **Smoking:** Yes/ No **Surgical History: _________________**

**SECTION 2**

**NECK DISABILITY INDEX:**

This questionnaire is designed to enable us to understand how much your neck pain has affected your ability to manage in everyday life. Please answer every section and mark in each section only once, which applies to you. We realize you may consider that two of the statements in any section may relate to you, but please just mark one which most closely described your problem.

| **Section 1 : Pain Intensity** | **Pre** | **Post** |
| --- | --- | --- |
| 0. I have no pain at the movement. |  |  |
| 1. The pain is very mild at the movement. |  |  |
| 2. The pain is moderate at the movement. |  |  |
| 3. The pain is fairly severe at the movement. |  |  |
| 4. The pain is very severe at the movement. |  |  |
| 5. The pain is the worst imaginable at the movement. |  |  |
| **Section 2 : Personal Care** |  |  |
| 0. I can look after myself normally without causing extra pain. |  |  |
| 1. I can look after myself normally but it causes extra pain. |  |  |
| 2. It is painful to look after myself and I am slow and careful. |  |  |
| 3. I need some help but manage most of my personal care. |  |  |
| 4. I need help everyday in most aspects of self care. |  |  |
| 5. I do not get dressed; I wash with difficulty and stay in bed. |  |  |
| **Section 3 : Lifting (Skip if you have not attempted lifting since the onset of your neck pain)** |  |  |
| 0. I can lift heavy weights without extra pain. |  |  |
| 1. I can lift heavy weights but it gives extra pain. |  |  |
| 2. Pain prevents me from lifting heavy weights off the floor, but I can manage if they are conveniently positioned eg. On a table. |  |  |
| 3. Pain prevents me from lifting heavy weights but I can manage light to medium weight if they are conveniently positioned. |  |  |
| 4. I can only lift very light weights. |  |  |
| 5. I cannot lift or carry anything at all. |  |  |

| **Section 4 : Reading** |  |  |
| --- | --- | --- |
| 0. I can read as much as I want to with no pain in my neck. |  |  |
| 1. I can read as much as I want to with slight pain in my neck. |  |  |
| 2. I can read as much as I want with moderate pain in my neck. |  |  |
| 3. I cannot read as much as I want because of moderate pain in my neck. |  |  |
| 4. I can hardly read at all because of severe pain in my neck. |  |  |
| 5. I cannot read at all. |  |  |
| **Section 5 : Headache** |  |  |

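### The Neck Disability Index form tells patients both to answer every section and to skip lifting, so totals may rest on different numbers of sections; the pain item is also ambiguously worded (minor)

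*Protocol*

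**What the plan says.** The Objectives section of the protocol lists disability among the things to be compared. The section on the NDI says "Neck disability will be assessed by using neck disability index" and gives nothing further on scoring.

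The form itself is in the questionnaire, Section 2, with a Pre and a Post column. Its general instruction is "Please answer every section and mark in each section only once, which applies to you". The lifting item is headed "Section 3 : Lifting (Skip if you have not attempted lifting since the onset of your neck pain". Options in each section are numbered 0 to 5; for lifting the last is "5. I cannot lift or carry anything at all". The first pain option reads "0. I have no pain at the movement", and the other five end in the same phrase, under a heading about pain intensity. The form as available stops at the heading of its fifth section.

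Under Outcome measures, the main outcomes are "pain intensity measured on VAS, endurance measured by cranio cervical flexion test and range of motion measured on inclinometer", and quality of life is among the secondary ones. The NDI is in neither list.

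The Data analysis procedure compares arms with a t-test or Mann-Whitney test at each assessment, and uses repeated measures ANOVA or Friedman within each group.

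**The concern.** The two completion instructions conflict for any patient who has not lifted since onset. Under the general instruction that patient marks an option, possibly one of the worst. Under the item heading the same patient leaves a blank. Which of these happens depends on the patient's reading of the form and not on disability.

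The skip also works in one direction over time. Its condition is "Skip if you have not attempted lifting since the onset of your neck pain", so it lapses once lifting has been tried. A patient may properly omit the item at Pre and answer it at Post, but not the reverse. A within-patient comparison can then set a total on fewer sections against a total on more.

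This arises when the patient fills in the form. An analysis plan can choose how to score a blank, but it cannot recover an answer that the form told the patient to leave out.

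The pain item is a separate and smaller fault. The phrase in "I have no pain at the movement" can be taken as pain on moving or as pain now, and patients may answer on different bases.

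**Working it through.** The protocol states no NDI figure, so there is nothing to reproduce. The check is score arithmetic.

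**Inputs.** From the form: each section is scored 0 to 5. Assumed, because the form is cut off: ten sections, maximum 50. Also assumed, because no scoring rule is shown: either (a) a raw sum with a blank counted as 0, or (b) proration to the maximum of the sections answered.

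**Notation.** S0 and S1 are the sums of the nine other sections at Pre and Post, g = S0 − S1 is the gain on them, and L is the lifting score at Post. Lifting is skipped at Pre.

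**Two equally disabled patients, one visit.** Under (a), skipping in place of a true lifting answer of 0 to 5 lowers the total by 0 to 5 points, or 0 to 10% of 50. If a proportion p of patients skip, the group mean is understated by p times their average unrecorded lifting score, at most 5p points. The protocol gives no basis for p.

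**One patient, Pre to Post.**

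- Under (a), the total rises when S1 + L > S0, that is, when L > g. As L is at most 5, only gains of 1 to 4 points can be reversed.
- Under (b), the score rises when (S1 + L)/50 > S0/45, that is, when L > g + S0/9. This condition is stricter.
- With change based on the nine sections answered at both visits, S1/45 is compared with S0/45, and the direction is always that of g.

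| S0 | S1 | L | Raw sum | Prorated | Common sections only |
|---|---|---|---|---|---|
| 18 | 15 | 4 | 18 to 19 (36% to 38%) | 18/45 = 40.0% to 19/50 = 38.0% | 40.0% to 15/45 = 33.3% |
| 18 | 17 | 4 | 18 to 21 (36% to 42%) | 40.0% to 21/50 = 42.0% | 40.0% to 17/45 = 37.8% |
| 18 | 13 | 4 | 18 to 17 (36% to 34%) | 40.0% to 17/50 = 34.0% | 40.0% to 13/45 = 28.9% |

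The first row is reversed by the raw sum and not by proration. The second is reversed by both. The third is reversed by neither, because the gain of 5 exceeds the lifting score of 4.

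Over all combinations with S1 < S0, 440 are reversed under (a) and 160 under (b). These are counts of possible scores and not probabilities.

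**Which planned comparisons are touched.** A patient who skips at Pre and answers at Post has an incomplete Pre score and a complete Post score. The baseline comparison and the within-group analysis are therefore exposed. The comparison of arms at Post is not affected by this route.

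**Pain item.** The wording is the same for the Pre and Post columns, and the protocol shows one form for all patients. It adds no term to any of the differences above.

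**The case against.** The strongest reply is that the consequence depends on a scoring rule nobody has seen. The form is cut off, a scoring key may follow, and a statistical analysis plan may deal with unanswered sections; its absence here is no finding. Proration would remove most of the reversals. This stands, and it limits what can be said about size. It does not remove the contradiction on the form, and the second row of the table shows that proration alone leaves a remainder.

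It can also be said that few patients will skip. Eligible patients have kept the movement of the upper limb, the protocol describes them as busy working people, and the form offers strongly limited patients their own options. That is fair: no skip rate can be inferred.

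A reader might infer three stronger things that the documents do not support.

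- *NDI scores are not comparable between visits or patients.* That would need a known scoring rule and actual skipping. The documents support only that they may not be comparable. Nor does a patient who skips at Pre and later scores lifting 1 to 3 simply worsen by 1 to 3 points: a rise of that full size needs no gain on any other section.
- *The comparison between arms is biased towards no effect.* The plan compares arms at each assessment, and a patient who answers at Post has a complete Post score. Bias there would need patients still skipping at Post, at rates that differ by arm, and nothing in the protocol points to that.
- *The pain wording makes visits non-comparable.* It is identical at both visits and cannot cause a reversal. Pain is also measured separately on the VAS.

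**Conclusion.** The contradiction is on the face of the form and the pain item is ambiguous; both need correcting. Lifting may be missing for some patients and visits, so NDI totals may rest on different numbers of sections, with possible distortion of the baseline and within-group results.

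For one patient at one visit, the error is at most 5 of an assumed 50 points under a raw sum. An apparent worsening in a patient who improved on the other nine sections is possible only for gains of 1 to 4 points, and only when the Post lifting score is larger than the gain. All this rests on ten 0-5 sections and on the scoring rules assumed above. No effect at group level can be estimated, because the frequency of skipping is unknown, and no directional bias between arms is shown.

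The point is minor. Disability is a stated objective and the NDI is the only instrument named for it, but the NDI is not among the listed main or secondary outcomes.

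**What to change.** Before the form is used:

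1. Remove the skip text from the lifting heading, so that lifting is answered like every other section.
2. If the text must stay, amend the general instruction to agree with it, score the NDI as a percentage of the maximum for the sections answered, and base within-patient change on sections answered at both visits. Proration alone is not enough.
3. In all six pain options, change 'movement' to 'moment', after checking the wording against the source instrument.

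The cost is a reprinted form and, if the skip stays, a sentence on scoring. No extra visits, patients or staff are needed.
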